### Data collection timeline

2.4.

Data collection is expected to be conducted from January 2023 to September 2023, though, this period may be extended to ensure a sufficient sample number, if necessary. Once recruitment begins, all potential participants will be invited to enter the observational study. The study aims and procedures will be explained in detail and in a simple and understandable manner to the potential participants, so that they can make an informed decision, on whether to accept or decline to participate. When a potential participant agrees to join the study, they are required to provide written informed consent. Only after this initial step will data be collected to assess the eligibility of participants.

Data will be collected from eligible adults in three visits, each one with an expected duration of about 1 h. Figure 1 summarizes the study design, including the data and samples to be collected at each time point of the observational study.

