Current evidence indicates that there is a reciprocal interaction between metabolism and the circadian system. Primarily, a comprehensive neural network connects the suprachiasmatic nucleus (SCN) of the hypothalamus to the energetic centers implicated in, for example, food intake, sleep/wakefulness and energy expenditure (17). The effect of the circadian system on metabolism, mediated by the SCN and peripheral clocks, is reflected in the circadian fluctuations exhibited by several metabolically significant hormones (17, 18). Changes in hormonal rhythms might lead to internal malfunction and are related to metabolic dysfunctions that predispose the development of metabolic diseases such as obesity (18–22). While the SCN is mainly synchronized by light/dark cycles, peripheral clocks are entrained by feeding/fasting cycles (23, 24). Besides meal timing, nutrients can also induce phase shifts in the peripheral circadian clock. Hirao and colleagues found that a combination of carbohydrates and protein is necessary to change the mouse liver clocks (25). As reviewed by Oike and colleagues (26), nutrients such as glucose and amino acids quickly alter the expression of clock genes, particularly Per2 and Rev-erbα (27–30). Skipping breakfast or having a lower food intake in the first meal of the day alongside with high-caloric dinners impairs peripheral clock gene expression and results in higher daily glucose excursions in animals (31–33). A study conducted by Jakubowicz and colleagues on individuals with type 2 diabetes showed that calories consumed at breakfast or dinner affected the daily rhythm of postprandial glycaemic excursion and insulin levels (34). These authors also reported that skipping breakfast negatively affected clock and clock-controlled gene expression (35).

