### Participant selection

2.2.

Participants will be recruited from healthcare centers in Leiria, Portugal. The study will also be disseminated through social networks and institutional emails, in an attempt to reach more participants.

The eligibility of the participants will be assessed on the first visit by the assessment of inclusion and exclusion criteria after the potential participants signed the informed consent. The observational study will be conducted on adults and recruitment will be gender-independent. Obesity will be defined according to the criteria of the World Health Organization (1). The detailed participant inclusion and exclusion criteria are listed in Table 1.

**Table 1 tab1:** Inclusion and exclusion criteria for the participants in both study groups.

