**Exclusion criteria**
Individuals unwilling or unable to give their informed consent. Severe psychiatric conditions and/or inability to understand and engage in the study. Night or rotating shift workers, or individuals that crossed more than two times zones in the 2 weeks before the beginning of the study. Diagnosed sleep disorders, including severe Obstructive Sleep Apnea. Pregnant women^1^. Individuals with an electronic medical device/implant^1^. Infection 4 weeks before baseline assessment. Regular use (equal to or greater than weekly) of the following medications: Wakefulness-promoting agents modafinil, amphetamine derivates, methylphenidate. Sedatives including benzodiazepines, Z-drugs (zopiclone, zolpidem and zaleplon). Melatonin, including circadian and melatonin analogs. Clonazepam and other drugs for nocturnal movement disorders. Probiotics. Anti-obesity drugs (orlistat, liraglutide). Glucocorticoids.

1 Assessment of body composition with the bioelectrical impedance analysis (BIA) equipment is not possible in these conditions.

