#### Biochemical assessments

2.5.2.

Peripheral blood samples (15–20 mL) will be collected from the participants at 08:00 a.m., after overnight fasting, and 04:30 p.m. on the same day, and aliquoted into EDTA tubes following safety standards, by certified healthcare professionals. Another blood sample (2.5 mL) will be collected from volunteers to PAXgene® Blood RNA Tubes (BD Biosciences), to obtain total RNA from whole blood.

For the total RNA from peripheral blood mononuclear cells (PBMC), blood samples will be diluted in 25 mL of Phosphate Buffered Saline (PBS) 1 × and added to 50 mL falcon tubes with 10 mL of Histopaque, density 1.077 g/mL. Samples will be centrifugated at 20^°^C to 22^°^Cand plasma will be immediately aliquoted and stored at −80^°^C. The interface bands, which contain the PBMC, will be aspirated into new 50 ml falcon tubes and washed with PBS 1 ×, followed by centrifugation at 21^°^C–25^°^C. Supernatants will be discarded and PBMC aliquots will be stored at −80^°^C until the analysis.

For the total RNA from whole blood, PAXgene® Blood RNA tubes will be centrifuged at 20 to 22°C and the supernatant removed. To the pellet, RNase-free water will be added and the samples vortexed until the pellet dissolution, followed by a centrifugation at 20^°^C to 22^°^C. After removal of the supernatant, a lysis buffer will be added, the sample vortexed and transferred to a 1.5 mL microcentrifuge tube where 40 μL of proteinase K will be added. After incubation, the sample will be transferred to a spin column of the Macherey Nagel RNA extraction kit, according to the manufacturer’s instructions. RNA concentration and purity will be determined using a spectrophotometer. Samples will be stored at −80^°^C until the analysis.

RNA samples will then be converted into cDNA and the mRNA levels of the clock genes (BMAL1, CLOCK, PER1-3, CRY1-2, CSNK1ε, REV-ERBα, REV-ERBβ, and DEC1) will be assessed using real-time quantitative reverse transcriptase polymerase chain reaction (qRT-PCR). Relative gene expression will be calculated according to the ΔCT method (51, 52).

Plasma levels of insulin, leptin, adiponectin, ghrelin, c-reactive protein, and interleukin-6 will be quantified using ELISA kits, according to the manufacturer’s instructions. Glucose will be assessed using the hexokinase method with a commercial kit.

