The conversion of food into energy and nutrients will be based on the Portuguese Food Composition Table (54), incorporated into the app and, if necessary, other food composition tables. In the app’s food diary section, participants can also upload pictures of the nutritional information/food labeling of the food items being consumed, if available. In the backoffice, it is possible to continuously adapt and complete the information on the Portuguese Food Composition Table by adding nutritional information for new food items or meals. The Portuguese Food Frequency Questionnaire (FFQ) is a validated semi-quantitative instrument that assesses dietary intake, reporting the previous 12 months. This tool will be used to collect information on the consumption of less frequently eaten foods and, therefore, minimize interferences with the day-to-day variation of food intake (55). The Portuguese FFQ includes a pre-determined list of 86 food items or groups, and nine frequency categories ranging from “Never or less < 1 per month” to “6+ per day” (56). Food consumption is quantified by multiplying the reported intake frequency by the food item or group average standard portion, and by a seasonal variation factor for items consumed only in a specific season. The conversion to nutrients will be supported by a compilation of databases on the nutritional food composition, including the Portuguese Food Composition Table (54).

The data collected with the FFQ will be mainly used to perform a global characterization of the participants’ dietary intake in the previous 12 months. The data collected using the 3-day food diary will be used to correlate dietary intake and circadian biomarkers.

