#### Questionnaires

2.5.5.

To complete the participant’s characterization and data, a set of validated questionnaires and instruments will be used.

The Pittsburgh Sleep Quality Index (PSQI) is a 19-items (plus 5 additional items, in case the responder has a roommate or bed partner, that do not contribute to the total score) self-reported questionnaire, designed to subjectively assess global sleep quality based on the participant’s retrospective evaluation (considers the usual sleep habits over the past one-month period). The items of the PSQI are divided into seven components, namely, subjective sleep quality, sleep latency, sleep duration, habitual sleep efficiency, sleep disturbances, use of sleeping medication, and daytime dysfunction, each weighted equally on a scale from 0 to 3. The global PSQI score ranges from 0 to 21, corresponding to the sum of the seven components. A global PSQI score greater than 5 indicates major difficulties in at least two components or moderate difficulties in more than three components (57, 58). This instrument has been validated for the Portuguese population (59).

The Munich Chronotype Questionnaire (MCTQ) was developed by Roenneberg and colleagues to assess the circadian phase of entrainment, which is considered a quantifiable biological phenotype (41, 60). The questions aim to evaluate sleep behavior on workdays and work-free days, separately, since this distinction is essential to determine the participant’s chronotype. The chronotype resultant from the MCTQ is expressed in local time and it is based on the Mid-Sleep time in Free days (MSF) after correction for potential compensatory sleep (MSF_sc_) (60). The midpoint of sleep has been considered one of the most accurate behavioral markers to determine the circadian phase (60, 61). However, to account for the sleep debt as a cofounder, it is necessary to calculate the average sleep duration of the entire week and correct MSF by subtracting half of the oversleep. According to the results of the MCTQ database, Roenneberg and colleagues identified seven groups based on MSF_sc_, namely, extremely early, moderately early, slightly early, intermediate, slightly late, moderately late and extremely late (60). This instrument has already been validated for the Portuguese population (62).

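### Nothing keeps cases and controls on the same calendar over a January to September window, so if the two groups fill at different times of year, season and the clock change could be read as an obesity effect

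*Protocol article*

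**What the plan says.** All references are to the protocol article.

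- **Window (2.4).** "Data collection is expected to be conducted from January 2023 to September 2023, though, this period may be extended", the reason given being to reach a sufficient number.
- **Enrolment (2.4, 2.2).** "Once recruitment begins, all potential participants will be invited to enter the observational study". Recruitment is through healthcare centres, and "The study will also be disseminated through social networks and institutional emails, in an attempt to reach more participants". No sentence pairs or balances cases and controls by date.
- **Chronotype (2.5.5).** "The chronotype resultant from the MCTQ is expressed in local time", as mid-sleep on free days corrected for oversleep (MSFsc).
- **Blood (2.5.2).** Samples "will be collected from the participants at 08:00 a.m., after overnight fasting, and 04:30 p.m. on the same day".
- **Premise (Introduction).** "While the SCN is mainly synchronized by light/dark cycles, peripheral clocks are entrained by feeding/fasting cycles".
- **Existing safeguard (Table 1).** Shift workers are excluded, as are "individuals that crossed more than two times zones in the 2 weeks before the beginning of the study". Season and the change to summer time are not covered.
- **Analysis (2.6).** The groups are compared by an independent-samples t-test or a Mann-Whitney test, with no covariate.
- **Limitations (Discussion).** Geography, self-report, drop-out and the two sampling times are named. Season is not.

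**The concern.** The study asks whether circadian measures differ between people with and without obesity. By the protocol's own account, light is the main cue for the central clock. Over nine months or more, both day length and the relation between clock time and sunrise change, so the same local-time MSFsc or the same 08:00 draw does not mean the same thing in January and in June.

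That matters for the group contrast only if the two groups are measured at different times of year. The plan does not intend this, but it does nothing to prevent or detect it. One group may fill faster than the other, and an extension used to complete the slower group would place its late members in a different season. An unadjusted two-group test would then attribute a calendar difference to obesity. The MCTQ would not resolve the doubt: the Discussion adds it to offset the weakness of two blood time points, yet it is exposed to the same calendar.

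**Working it through.** **Inputs from the protocol.** Two-sided alpha 0.05. The sample size in 2.3 reproduces: (0.18 × 0.82 + 0.55 × 0.45) × (1.96 + 0.84)² / 0.37² = 0.3951 × 7.84 / 0.1369 = 22.63, so 23 per group. The figure after the attrition allowance is 32 per group. Both are used below.

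**Inputs assumed, not in the documents.** Seasonal shift in local-time MSFsc, s = 0.25, 0.5 or 1 h. Within-season SD = 1 or 1.5 h. Share measured before the clock change: 60% in one group, 20% in the other. No true obesity effect.

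**Formulae.**
- Spurious difference: Δ = s × (0.60 − 0.20)
- Variance in a group with share f before the change: V = SD² + s² f(1 − f)
- SE = √[(V₁ + V₂)/n]
- False-positive rate = Φ(Δ/SE − 1.96) + Φ(−Δ/SE − 1.96)

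**Upper end** (s = 1 h, SD = 1 h, n = 32): Δ = 0.40 h = 24 min; V₁ = 1.24, V₂ = 1.16; SE = √(2.40/32) = 0.274; ratio 1.46; rate 0.31.

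**Lower end** (s = 0.25 h, SD = 1.5 h, n = 23): Δ = 0.10 h = 6 min; SE = 0.444; ratio 0.225; rate 0.056.

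| s (h) | Δ (min) | SD 1 h, n = 23 | SD 1 h, n = 32 | SD 1.5 h, n = 23 | SD 1.5 h, n = 32 |
|---|---|---|---|---|---|
| 0.25 | 6 | 6% | 7% | 6% | 6% |
| 0.5 | 12 | 10% | 12% | 7% | 8% |
| 1 | 24 | 24% | 31% | 14% | 18% |

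**Enrolment independent of season.** With a full 1 h shift, SD 1 h and each person equally likely to fall on either side, simulated t-tests reject in about 5% of studies at both 23 and 32 per group. Season is then part of the within-group variance.

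**Chance imbalance.** With half of each group expected on each side, the SD of the difference in shares is √(0.5/n): 0.147 at n = 23 and 0.125 at n = 32. A difference of 0.4 or more arises by chance in about 0.5% of studies at n = 23 and 0.2% at n = 32. The table therefore describes systematic separation, not bad luck.

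**Is one before/after step a fair model?** Assuming Leiria lies near 39.7° N, 8.8° W and summer time starts in late March, solar geometry gives:

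| Date | Day length (h) | 08:00 draw, hours after sunrise |
|---|---|---|
| 10 January | 9.5 | 0.1 |
| Just before the March change | 12.3 | 1.5 |
| Just after the March change | 12.4 | 0.5 |
| 20 June | 15.0 | 1.9 |
| Late September | 12.0 | 0.5 to 0.6 |

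Lengthening days and the clock change pull in opposite directions. The net seasonal effect on a local-time measure is not a single step, and neither its size nor its sign is known from the documents. The first table is an illustration only, and an adjustment needs day length and summer time as separate terms.

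**The case against.** The strongest reply is that the mechanism is not in the plan. Invitation is open to everyone from the start, and the recruitment channels are listed for all participants. A reader might infer that cases come from healthcare centres and controls from social networks and e-mail, at different rates. The article assigns no channel to a group, so that is conjecture. It stands as an objection: separation of the calendars is possible, not planned.

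A reader might also infer that ordinary chance imbalance in season inflates the error rate. It does not, as the simulation shows.

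Nor can 31%, or any rate from a more extreme split, be read as the study's expected false-positive rate. Split, shift and SD are all assumed, and a small shift leaves the rate near 6% to 7%.

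The food frequency questionnaire multiplies intake "by a seasonal variation factor for items consumed only in a specific season". That might be taken to show that season was considered for diet and overlooked for chronotype, but it is routine scoring for seasonal foods and proves neither.

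Finally, a season covariate or visit scheduling could sit in a fuller protocol or analysis plan that is not shown, and the timeline figure is missing. This has some force for the covariate. It has less for enrolment: section 2.4 sets the window and the invitation rule, and a later analysis plan cannot restore overlap between groups recruited months apart.

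**Conclusion.** The concern holds in conditional form. The window, the local-time chronotype, the clock-time draws and the unadjusted comparison are all stated, and no step keeps the groups on the same calendar or measures whether they were. If the groups fill at different times of year, or one is topped up during an extension, the stated comparison cannot separate season from obesity. If enrolment is independent of season, the test keeps its 5% level and season costs only precision.

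For a 60%/20% split, the false-positive rate is about 6% to 31%, assuming a 0.25 to 1 h shift, SD 1 to 1.5 h and 23 to 32 per group. None of split, shift or SD comes from the documents. The documents do not support saying that the study will be biased. They do support saying that a nearly free safeguard is absent from the stated design and analysis.

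**What to change.** **Section 2.6.** Compare chronotype and the circadian and metabolic biomarkers by regression on group, adding day length on the date of the relevant visit and an indicator for summer time. Both follow from the date alone. Keep the unadjusted test as a sensitivity analysis. Report MSFsc and draw times in standard time as well as local time, and tabulate visit dates by group so that calendar overlap can be seen.

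**Section 2.4.** State that both groups will be recruited concurrently where practical, including during any extension, without holding back willing participants. Delaying the faster group or closing weeks around the clock change would give tighter control, but the Discussion already expects difficult recruitment and high drop-out, so neither is asked for here.

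**Cost.** One or two degrees of freedom, a few lines of protocol text and no extra visits, samples or participants. The limit is that if the groups barely overlap in time, adjustment rests on extrapolation and helps little; the table of dates would show this.

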**Figure 1 fig1:**
[figure not shown]
Data collection time points and sample collections for the participants of the observational study. Icons made by Freepik from www.flaticon.com. Icons made by iconixar from www.flaticon.com. Icons made by Sweetline from www.flaticon.com.

### Measurements

2.5.

#### Anthropometric and body composition assessments

2.5.1.

Participants’ body weight, height, and waist circumference will be measured according to the Portuguese Directorate General of Health guidelines for anthropometric procedures in adults (49). Body mass index (BMI; kg/m^2^) will be calculated and categorized according to the age and sex-specific BMI cut-offs for adults (50). Fat mass (FM), visceral adipose tissue (VAT), fat-free mass (FFM), and skeletal muscle mass (SMM) for arms, legs, torso, and whole body will be assessed using the bioimpedance equipment seca mBCA 525 (Bacelar, Porto, Portugal).

#### Biochemical assessments

2.5.2.

Peripheral blood samples (15–20 mL) will be collected from the participants at 08:00 a.m., after overnight fasting, and 04:30 p.m. on the same day, and aliquoted into EDTA tubes following safety standards, by certified healthcare professionals. Another blood sample (2.5 mL) will be collected from volunteers to PAXgene® Blood RNA Tubes (BD Biosciences), to obtain total RNA from whole blood.

For the total RNA from peripheral blood mononuclear cells (PBMC), blood samples will be diluted in 25 mL of Phosphate Buffered Saline (PBS) 1 × and added to 50 mL falcon tubes with 10 mL of Histopaque, density 1.077 g/mL. Samples will be centrifugated at 20^°^C to 22^°^Cand plasma will be immediately aliquoted and stored at −80^°^C. The interface bands, which contain the PBMC, will be aspirated into new 50 ml falcon tubes and washed with PBS 1 ×, followed by centrifugation at 21^°^C–25^°^C. Supernatants will be discarded and PBMC aliquots will be stored at −80^°^C until the analysis.

For the total RNA from whole blood, PAXgene® Blood RNA tubes will be centrifuged at 20 to 22°C and the supernatant removed. To the pellet, RNase-free water will be added and the samples vortexed until the pellet dissolution, followed by a centrifugation at 20^°^C to 22^°^C. After removal of the supernatant, a lysis buffer will be added, the sample vortexed and transferred to a 1.5 mL microcentrifuge tube where 40 μL of proteinase K will be added. After incubation, the sample will be transferred to a spin column of the Macherey Nagel RNA extraction kit, according to the manufacturer’s instructions. RNA concentration and purity will be determined using a spectrophotometer. Samples will be stored at −80^°^C until the analysis.

RNA samples will then be converted into cDNA and the mRNA levels of the clock genes (BMAL1, CLOCK, PER1-3, CRY1-2, CSNK1ε, REV-ERBα, REV-ERBβ, and DEC1) will be assessed using real-time quantitative reverse transcriptase polymerase chain reaction (qRT-PCR). Relative gene expression will be calculated according to the ΔCT method (51, 52).

Plasma levels of insulin, leptin, adiponectin, ghrelin, c-reactive protein, and interleukin-6 will be quantified using ELISA kits, according to the manufacturer’s instructions. Glucose will be assessed using the hexokinase method with a commercial kit.

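### As section 2.5.2 is written, the only stored plasma is taken after dilution in 25 mL PBS, no dilution correction is stated, and the upper draw volume overfills the tube

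*Protocol article*

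**What the plan says.** All of this is in section 2.5.2 (Biochemical assessments) of the protocol article.

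- **Draw:** "Peripheral blood samples (15–20 mL) will be collected from the participants at 08:00 a.m., after overnight fasting, and 04:30 p.m. on the same day", into EDTA tubes. The volume is a range.
- **Dilution:** in the paragraph on RNA from mononuclear cells, "blood samples will be diluted in 25 mL of Phosphate Buffered Saline (PBS".
- **Gradient:** the diluted blood is then "added to 50 mL falcon tubes with 10 mL of Histopaque, density 1.077 g/mL" and centrifuged.
- **Plasma:** after that spin, "plasma will be immediately aliquoted and stored at −80" °C. The interface bands holding the mononuclear cells are aspirated next.
- **Assays:** "Plasma levels of insulin, leptin, adiponectin, ghrelin, c-reactive protein, and interleukin-6 will be quantified using ELISA kits". For glucose, "Glucose will be assessed using the hexokinase method with a commercial kit"; the specimen is not named.

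The supernatants of the later cell wash are discarded. The only other blood is the 2.5 mL PAXgene tube, which is for RNA. The article mentions no plasma set aside before dilution, no recorded blood volume, no haematocrit and no correction of the assay results.

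**The concern.** In the order described, the layer frozen as plasma is plasma mixed with PBS. A laboratory that followed the text and assayed that layer without correction would report concentrations several-fold below the true ones. The PBS volume is fixed while the plasma volume depends on how much blood goes in and on the participant's haematocrit, so the error would differ from person to person.

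The metabolic markers matter to this study. The Introduction names adiponectin, leptin and insulin among the measures that most earlier studies lack, and the Discussion presents the joint measurement of dietary, circadian and metabolic markers as an advantage. Values that are too low by an unrecorded factor could not be set beside those of other studies. Once samples are frozen without a recorded volume, the factor cannot be recovered.

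**Working it through.** The article states no dilution factor, so there is no figure of its own to reproduce. The check is a volume balance.

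**Inputs from section 2.5.2:** blood volume V = 15 to 20 mL; PBS 25 mL; Histopaque 10 mL; tube 50 mL.

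**Assumptions, not in the article:** haematocrit h from 0.36 to 0.50; the whole draw goes into one 25 mL dilution; PBS mixes only with the plasma compartment.

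**Formula:** plasma volume Vp = V × (1 − h); dilution factor = (Vp + 25) / Vp. The measured concentration is the true one divided by this factor.

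Example at h = 0.45:
- V = 15 mL: Vp = 8.25 mL, factor = 33.25 / 8.25 = 4.03.
- V = 20 mL: Vp = 11 mL, factor = 36 / 11 = 3.27.

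| Haematocrit | Factor, 15 mL | Factor, 20 mL | Ratio 15 to 20 mL |
|---|---|---|---|
| 0.36 | 3.60 | 2.95 | 1.22 |
| 0.40 | 3.78 | 3.08 | 1.23 |
| 0.45 | 4.03 | 3.27 | 1.23 |
| 0.50 | 4.33 | 3.50 | 1.24 |

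The range is 2.95 to 4.33.

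**Variation.** At equal haematocrit, two people with the same true level would differ by 22–24% if one gave 15 mL and the other 20 mL. With the volume fixed at 15 mL, the factor still runs from 3.60 to 4.33, a ratio of 1.20, through haematocrit alone.

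**Dependence on the haematocrit assumption.** Even with h set to zero, the factor would be (V + 25) / V: 40 / 15 = 2.67 and 45 / 20 = 2.25. Under the single-dilution assumption the conclusion of a large dilution does not rest on the haematocrit chosen; its exact size does.

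**Do the volumes fit one tube?** At 15 mL: 15 + 25 + 10 = 50 mL, which just fills it. At 20 mL: 20 + 25 + 10 = 55 mL, which does not fit. The article does not say how a larger draw is shared over tubes, and the answer changes the factor:
- If the draw is diluted once and the mixture is shared over tubes, the table stands.
- If the draw is halved and each half gets its own 25 mL PBS, Vp per tube is smaller. For 10 mL per tube the factor is 4.91 to 6.00; for 7.5 mL per tube it is 6.21 to 7.67.
- If a fixed part of every draw is diluted, variation with draw volume disappears and only variation with haematocrit remains.

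**Effect on the planned analyses.** Section 2.6 plans t-tests or Mann–Whitney tests and Pearson or Spearman correlations. Multiplying every value by the same constant changes none of these statistics or a ratio of group means. Only the varying part of the factor enters the comparisons: as added noise, or as bias if blood volume or haematocrit is distributed differently in the two groups.

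**The case against.** The strongest reply is that this is a condensed article. It also leaves out spin speeds, spin times and aliquot volumes, so a neat EDTA aliquot or a back-correction may well stand in the full protocol or a laboratory procedure. The dilution paragraph is introduced as the route to mononuclear-cell RNA, the blood goes into more than one EDTA tube, and the assay paragraph does not name the aliquot used. This stands as a limit on certainty: the text shows what is described, not what the laboratory does. It does not remove the point, because the article does more than stay silent. It gives an explicit order in which plasma is collected after dilution, and it names no other plasma.

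Three stronger readings are tempting, and the article does not support them.

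- **That the results will be 3–4 times too low, with a 23% spread between people.** Both figures need an assumed haematocrit and the whole draw in one dilution. The article states neither, and 20 mL does not fit one tube.
- **That the comparison of obesity and control groups is biased.** Nothing in the article shows that blood volume or haematocrit differs by group, and a common dilution cancels in the planned tests and correlations.
- **That the circadian findings are compromised.** The group differences that the Discussion expects are in clock-gene expression, which is measured on RNA by the ΔCT method and is untouched by plasma dilution.

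Glucose is affected only if it is taken from the same aliquot. The article also applies no clinical threshold to these analytes, so misclassification against a cut-off is not at issue.

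**Conclusion.** The point holds as a defect in the described procedure. Followed literally, section 2.5.2 yields PBS-diluted plasma for insulin, leptin, adiponectin, ghrelin, C-reactive protein and interleukin-6, with no correction stated. Absolute levels would be about 3.0 to 4.3 times too low on the stated assumptions, and lower still if a split draw received 25 mL PBS in each tube. Participant-level error would be added. The tube volumes need reconciling whatever the laboratory does about plasma. This should be corrected, but it does not undermine the study's main expected comparisons. Confidence is medium, because an unstated neat aliquot cannot be excluded.

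**What to change.** Preferred: state that the plasma aliquot for the ELISAs, and for glucose if measured in plasma, is taken from centrifuged EDTA blood before any PBS is added, and that the cells then go on to the gradient step. This costs one extra spin of a tube already drawn and a line in the laboratory procedure, with no extra blood or visit. The laboratory should confirm that the added spin suits its mononuclear-cell work.

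Alternative: state a fixed blood volume per tube that fits with the PBS and Histopaque, record it for every sample, and back-correct each result for its own dilution. Because the factor depends on plasma volume, this correction also needs a haematocrit or a measured plasma volume; a recorded blood volume alone leaves the haematocrit part uncorrected.

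In either case, say how a 20 mL draw is divided over 50 mL tubes and name the specimen for glucose. If neat plasma is already taken, correcting the order of steps in section 2.5.2 settles the plasma question.
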